**Methods::**

In this multi-method study, we translated and cross-culturally validated the CRBS to Czech (CRBS-CZE) first through the following main steps: professional translation, reconciliation/harmonization, and cross-cultural adaptation, and piloting in 50 cardiac patients. A prospective study will be undertaken to psychometrically-validate the CRBS-CZE, where 300 to 600 cardiac inpatients eligible for phase II/outpatient CR will be recruited. Consenting participants will be informed about the CR program and their sociodemographic, clinical characteristics, and the CRBS-CZE administered. Factor analysis will be performed with oblique rotation, factors will be extracted based on eigenvalues, the examination of the scree plot, and factor loadings. The internal reliability of the total scale and subscales will be assessed with Cronbach alpha. Overall CRBS scores will be compared by patient characteristics such as sex, socioeconomic indicators, risk factor burden, and travel time to investigate content validity. Their CR enrollment, adherence (% of 24 prescribed sessions attended), and completion will be tracked. The second administration of CRBS-CZE will be undertaken in patients at 3 weeks after enrollment. To test criterion validity, *t* tests and Pearson correlation (for adherence) will be used to determine the association of these utilization indicators with CRBS scores.

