## Introduction

1

Cardiovascular diseases (CVDs) are the leading causes of death in the world, and are a significant burden in Central Europe in particular.^[1]^ These many cardiac patients are at increased risk for recurrent events.^[2]^ For example, CVDs are the most common reasons for hospitalization in the Czech Republic, as well as are common sick leave and disability causes.^[3]^ According to the Czech Statistical Office, 25.4 billion CZK was spent on CVDs treatment in 2016, which was 13.6% of all health care expenditures that year.^[4]^ These diseases also represent a severe socioeconomic problem for patients and their families. This is unfortunate, given, according to the World Health Organization, that nearly 75% of recurrent cardiovascular events may be prevented.^[5]^ Indeed, cardiac rehabilitation (CR) is an effective secondary preventive model of care to mitigate this burden.^[6]^ However, CR is grossly under-utilized worldwide, including in Central Europe.^[7]^

The reasons for under-utilization are well-established in high-resource settings such as Western Europe and North America, consisting of factors at the health system, provider, and patient levels.^[8–10]^ A recent review; however, reveals just how few studies have explored these barriers outside of these settings, even though the burden of CVDs is so much higher here.^[11]^

Validated scales such as the cardiac rehabilitation barriers scale (CRBS), to assess reasons for under-utilization are available in the English language.^[12]^ Despite being self-reported by patients, they can validly capture barriers at these multiple levels. Studies reveal key barriers include lack of perceived need/awareness, distance to center, and work conflicts. These are amenable to relatively simple mitigation efforts, and hence barrier identification in patients is essential to promoting their access and participation. The CRBS has now been translated into 14 languages.^[13]^ Studies in non-Western settings do reveal different barriers, barriers which again are ripe for mitigation, bolstering the importance of measuring these barriers in these settings.^[11]^

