Barriers to CR participation in the Czech Republic are still unknown or not adequately described, despite this great need for CR as outlined above, as in the whole Central Europe. The aim of the study is first to translate and cross-culturally adapt CRBS to Czech (CRBS-CZE), and then psychometrically-validate the translation. The study shall include an assessment of the structure of factors, internal reliability as well as validity (design and criterion).^[14]^ The second aim then is to identify the key barriers which prevent patients from entering phase II of CR (outpatient). Furthermore, we will describe the degree of CR utilization in the program, namely, enrollment, adherence, and completion.^[15]^

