### Setting

2.2

The prevalence of cardiovascular risk factors in the Brno region is high.^[16]^ This study will be undertaken at the UH Brno of the Czech Republic. Approximately 1000 patients are hospitalized in the Department of Internal Cardiology Medicine, where recruitment will take place annually. The physicians in the Department have an association with the CR program and are generally supportive of patients referrals.

The institution also has an outpatient CR program. It is a comprehensive program consisting of exercise and education of lifestyle, and it is delivered dominantly by physiotherapists. Indicated patients have to complete cardiopulmonary exercise test before CR enrollment and post-program. There is practically no waiting list, and patients commence CR approximately 4 to 12 weeks post-discharge, depending on their clinical status and preferences. It involves 3 sessions a week for 2 months (total 24 trainings). The health insurance company completely covers the CR program. There could be a problem with parking because of a few places.

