### Psychometric validation

2.4

Eligible patients in the Department of Internal Cardiology Medicine will be approached from January 2020 for 1 year. Consenting patients will be informed about CR and referred. A physiotherapist will provide a questionnaire to the participants assessing their characteristics as well as the CRBS-CZE and will assist them in completion as needed. Thus all data will be secured via self-report, interview with patients, measurement, and will also be extracted from charts where available. Patients’ enrollment, session attendance, and completion of the program will be tracked in the CR charts (this too will be extracted for the study 2 months later). At 3 weeks after enrollment participated, patients will complete CRBS-CZE for the second time. A flowchart of the study protocol is shown in Figure 1.

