### Analysis

2.9

The process of reconciliation/harmonization and cultural adaptation, piloting, and finalization will be documented in detail, and any associated revisions to items specified. For the psychometric validation, Statistica TIBCO (Software Inc, Palo Alto, USA) will be used, and *P* < .05 will denote statistical significance. First, data to characterize the sample will be processed via descriptive statistics – mean, standard deviation, as well as frequencies and percentages. We will consider the completeness of the scale by using content analysis to code any additional barriers reported by respondents. We will assess factor structure with maximum likelihood factor analysis with oblique rotation. Factors with Eigen values >1 will be extracted according to the Kaiser–Guttman criterion. The scree plot will also be considered to confirm the appropriate number of factors. Factor loadings >3 will be interpreted in terms of subscale determinations. To evaluate the internal reliability of CRBS-CZE, we will use Cronbach alpha. To compare barriers by utilization indicators to test criterion validity, we will use a *t* test and Pearson correlation, as applicable. To test construct validity, differences in CRBS total scores will be compared by the sociodemographic and clinical characteristics outlined above, using the same 2 tests as applicable. Finally, interpretation of highest subscale and item scores will ensure to identify key barriers in this setting.

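### The analysis assigned to aim 2 describes the highest barrier scores but does not link them to enrollment, although the aim concerns barriers that prevent entry

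*Protocol article*

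**What the plan says.** The Introduction of the protocol article sets the second aim: to "identify the key barriers which prevent patients from entering phase II of CR (outpatient"). Section 2.9 (Analysis) gives one step for it: "interpretation of highest subscale and item scores will ensure to identify key barriers in this setting". That sentence names no subgroup and does not mention enrollment.

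Enrollment is nevertheless recorded. Section 2.8 classes a patient as an enroller after at least one session by 12 weeks post-discharge, and everyone else as a non-enroller. Section 2.9 also compares barriers by utilization indicators with a t test or Pearson correlation, but gives criterion validity as the purpose.

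On procedures, section 2.4 says: "Consenting patients will be informed about CR and referred". The questionnaire is described next. The abstract gives the same order for information: "Consenting participants will be informed about the CR program and their sociodemographic, clinical characteristics, and the CRBS-CZE administered". Recruitment is of inpatients, and section 2.2 says that "patients commence CR approximately 4 to 12 weeks post-discharge".

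**The concern.** How strongly an item is endorsed and whether it separates patients who enter from those who do not are two different quantities. Aim 2 is worded in terms of the second; the analysis named for it delivers the first. The first questionnaire is completed in hospital, weeks before CR would begin, so the answers are anticipatory. Whether a patient entered becomes known only later, and the key-barrier step does not use that information.

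The study also acts on something it measures. The Introduction says: "Studies reveal key barriers include lack of perceived need/awareness, distance to center, and work conflicts". Informing every participant about CR before the scale is given may lower the awareness part of that list, and all participants are referred. The barriers found, and the enrollment rate, are then those of informed, referred patients.

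At stake is the list of key barriers, which the Discussion makes the starting point for further research on which strategies to use. The Discussion already expects commuting time to be among the most critical barriers. A distance item could score high whether or not it separates enrollers from non-enrollers, and the analysis as written would not show which is the case.

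**Working it through.** **1. The plan's own figure.** Section 2.5 asks for 10 participants per variable. With the 21 items of section 2.7, 10 × 21 = 210, as stated (the lower bound of 5 per variable gives 105). This figure is not in dispute. It concerns the factor analysis, not aim 2. The expected sample is 300 to 600.

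**2. The passages side by side.**
- Aim (Introduction): barriers that prevent entry.
- Analysis for the aim (2.9): highest subscale and item scores; no group named, enrollment not used.
- Analysis that uses enrollment (2.8, 2.9): comparison of barriers by utilization, for criterion validity; not stated to be by item, nor to inform the choice of key barriers.
- What a score means (2.7): the patient's perception of how far a barrier affects enrollment and participation. All items apply to enrollers and non-enrollers alike.

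A high score is therefore evidence of a perceived barrier. It does not show whether non-enrollers score higher than enrollers.

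**3. Can the two measures disagree?** Suppose the scores are averaged over all patients (the natural reading of 2.9, though not stated). With enrolling share s, the overall mean is s × (enroller mean) + (1 − s) × (non-enroller mean). The documents give neither s nor item means, so all values here are assumed.
- Item A: 3.5 in both groups, difference 0.
- Item B: 2.0 in enrollers and 3.2 in non-enrollers, difference 1.2.
- Overall mean of B at s = 10%: 0.1 × 2.0 + 0.9 × 3.2 = 3.08. At s = 50%: 0.5 × 2.0 + 0.5 × 3.2 = 2.60.

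A leads on the highest score throughout, and B leads on the difference. If A is 3.0 instead, A still leads at s = 40% (B is 0.4 × 2.0 + 0.6 × 3.2 = 2.72) but not at 10% (3.08). The order changes at s = (3.2 − 3.0)/1.2 = 1/6. Among non-enrollers only, B (3.2) leads when A is 3.0 but not when A is 3.5, so restricting to non-enrollers does not replace the difference. This shows that the measures can disagree, not how often or by how much they will.

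**4. Can the planned sample support a comparison by item?** Detectable standardized difference at 80% power, two-sided: d = (z_alpha + z_power) × √(1/n1 + 1/n2), with z_power = 0.842 and z_alpha = 1.960 at 0.05 or 3.038 at 0.05/21. Enrolling shares of 10% to 50% are assumed.

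| Patients | Enrolling | Enrollers / non-enrollers | d at 0.05 | d at 0.05/21 |
|---|---|---|---|---|
| 300 | 10% | 30 / 270 | 0.54 SD | 0.75 SD |
| 300 | 20% | 60 / 240 | 0.40 SD | 0.56 SD |
| 300 | 30% | 90 / 210 | 0.35 SD | 0.49 SD |
| 300 | 50% | 150 / 150 | 0.32 SD | 0.45 SD |
| 600 | 10% | 60 / 540 | 0.38 SD | 0.53 SD |
| 600 | 20% | 120 / 480 | 0.29 SD | 0.40 SD |
| 600 | 30% | 180 / 420 | 0.25 SD | 0.35 SD |
| 600 | 50% | 300 / 300 | 0.23 SD | 0.32 SD |

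For example, at 300 patients and 10%: (1.960 + 0.842) × √(1/30 + 1/270) = 2.802 × 0.1925 = 0.54. Without adjustment, 21 independent tests at 0.05 give a family-wise error of 1 − 0.95^21 = 0.66, so some control is needed.

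**The case against.** The case against is substantial, and much of it stands.

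- Section 2.9 says neither pooled nor mean, and an article may leave a breakdown by enrollment to the full protocol. That is fair. The point is not that detail is missing, but that the analysis stated for the aim measures something other than the aim.
- Scores will be related to enrollment. Section 2.9 speaks of barriers in that comparison and of total scores only in the next sentence, so an item or subscale comparison is not excluded. This stands, but the comparison is given a different purpose and is not tied to aim 2.
- A reader might infer that the plan cannot identify barriers to entry. The documents do not support this: the scale asks about perceived effect on enrollment, so high scores are relevant evidence, and the data for a linked analysis are collected.
- A reader might infer that an item scored equally by both groups prevents nothing. That is wrong. A barrier shared by all can lower entry for all and still show no difference. Ranking on the difference alone would discard it, and the difference is itself only an unadjusted association.
- A reader might infer that informing and referring patients removes the main barriers. The Introduction names awareness, together with perceived need, but not referral. The scale's item table is not shown. Section 2.2 says the physicians "are generally supportive of patients referrals", and no usual referral rate is given. The size of any effect is unknown.
- The Discussion does not choose interventions directly from these scores; it plans more research and testing first. This lowers the stakes but does not remove them.

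**Conclusion.** The point holds in a limited form. As written, the analysis assigned to aim 2 describes perceived barriers and does not show which of them distinguish patients who do not enter from those who do. The two can disagree, but the documents give no item means and no enrolling share, so the extent cannot be estimated; the example rests on assumed values. Awareness barriers may be understated by an unknown amount, and the results describe informed and referred patients. This is a cheap improvement that brings the analysis closer to the aim, not a flaw that invalidates the study. The planned 300 to 600 patients allow the comparison by item for moderate differences, if 10% to 50% enroll.

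**What to change.** For aim 2:

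1. Keep the description of the highest item and subscale scores, and report it for non-enrollers.
2. Add, for each item and subscale, the non-enroller minus enroller difference with a 95% CI, using Holm or false-discovery control over the 21 items.
3. Specify the first administration as the source. The text does not say which of the two supplies the scores, and the second, at 3 weeks after enrollment, would cover enrollers only if CR enrollment is meant.
4. Interpret the level and the difference together, as association, since a barrier shared by both groups can still matter.
5. State that aim 2 and the enrollment rate apply to informed and referred patients.

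The cost is a little more analysis and some wording, with no new data. The downside is limited precision per item, as tabulated above. The tabulated figures use Bonferroni; Holm is never less powerful. Wide intervals should be read as inconclusive, not as evidence that an item is unimportant.

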### Results of translation and cross-cultural validation of CRBS

2.10

The translation was completed in 2019 and is shown in Table 1. In the phase of reconciliation/harmonization and cultural adaptation, revisions in wording were made to the following items: 1 to 7, 10 to 11. Some example additions were made to specify these items, and for clarification, we added point 0 (not applicable) to the Likert scale. In the pilot phase, the patients reported the questions were generally clear, relevant, and comprehensive. There were no additional barriers raised, among non-enrollers or enrollers alike. Some other revisions in wording were made to the following items: 3, 7, and 16.

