### CRBS

2.7

This scale evaluates patients’ perception of the degree to which patient, provider, and health system-level barriers affect their CR enrollment and participation (all items applicable to enrollers and non-enrollers alike). The English version consists of 21 items (barriers), related to 4 subscales – healthcare system factors, logistical barriers, work/time conflicts, comorbidities/functional status (although some translations consist of 5 subscales). These items are rated on a 5-point Likert scale (1 – strongly disagree, 5 – strongly agree). Higher scores indicate greater barriers to CR. There is also an open-ended item at the bottom where patients are asked to report any additional factors. Criterion validity has been established in the English version and many of the translations, demonstrated by significant differences in CRBS scores by CR use.^[21,23]^

Where participants completed >80% of the items, a mean total score will be computed. Subscale scores will also be computed based on the results of the factor analysis.

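### A 'not applicable' answer was added as point 0 of the Czech scale, but the scoring and analysis rules were not adapted; scored as written, it falls below 'strongly disagree'

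*Protocol article*

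**What the plan says.** Section 2.7 (CRBS) introduces the source instrument: "The English version consists of 21 items (barriers"). It gives the response format as "These items are rated on a 5-point Likert scale (1 – strongly disagree, 5 – strongly agree") and the direction as "Higher scores indicate greater barriers to CR". The scoring rule follows: "Where participants completed >80% of the items, a mean total score will be computed". On subscales it says "Subscale scores will also be computed based on the results of the factor analysis".

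Section 2.10 then reports, among the adaptations made for the Czech version, that "for clarification, we added point 0 (not applicable) to the Likert scale".

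Section 2.9 (Analysis) lists what is done with the item responses. On structure it says "We will assess factor structure with maximum likelihood factor analysis with oblique rotation". It adds Cronbach alpha for reliability, and t tests or Pearson correlation of scores against utilization and patient characteristics. Key barriers are to be read from the items and subscales that score highest.

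No section shown says whether a 0 is a score, a missing value or a completed item.

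**The concern.** 'Not applicable' is a nominal answer. Placed at 0 on an ordered agreement scale, it becomes the lowest value if the numbers are used as they stand. The only scoring rule in the article was written around a 1 to 5 format and has no step that removes it.

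Four uses of the item responses are exposed:

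- **Total score.** Each 0 would pull the mean down, and by more than a 'strongly disagree' would.
- **Factor structure and alpha.** Items that do not apply to the same patients would move together because of the shared 0. The likely case is the work/time-conflict items in patients without a job. Section 2.6 collects work status, with occupational exertion only for the employed, so non-employed patients are expected. Subscales are built from this analysis.
- **Validity comparisons.** Section 2.8 compares scores by age and socioeconomic indicators, and section 2.9 by the sociodemographic characteristics generally. Use of 'not applicable' on work items plausibly tracks these.
- **Ranking of barriers.** An item that matters much to the patients it concerns could rank low because others marked it 0.

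Because the study exists to validate this instrument, the coding of an item response underlies every result. If the rule stays open, it could also be chosen after seeing which coding gives the neater factor structure.

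**Working it through.** **Inputs from the article.** There are 21 items, scored 1 to 5, with 0 added for 'not applicable'. The total is the item mean if more than 80% of items are completed. The plan's own factor-analysis figure in section 2.5 reproduces: 10 × 21 = 210, with 5 × 21 = 105 as its lower bound. So the plan does work with 21 items.

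**Inputs assumed.** The article gives none of these: the mean of a patient's applicable items, m = 2.0 to 2.5; the number of zeros, k = 2; item mean 2 and SD 1; the share q of patients to whom a pair of items does not apply.

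**1. Total score.** With k zeros included, total = m(21 − k)/21.

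- m = 2.0, k = 2: 2.0 × 19/21 = 1.810, a drop of 0.190.
- m = 2.5, k = 2: 2.5 × 19/21 = 2.262, a drop of 0.238.
- Against coding the two items as 1 instead of 0: 2 × 1/21 = 0.095, whatever m is.
- All applicable items at 1 and four zeros: 17/21 = 0.81, below the minimum possible on a 1 to 5 scale.
- Zeros left out of numerator and denominator: the total equals m, a shift of 0.

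**2. Induced correlation.** Take two items that are independent among the patients to whom they apply, with mean μ and variance v, and both coded c in the same share q of patients:

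r = q(1 − q)(μ − c)² / [(1 − q)v + q(1 − q)(μ − c)²]

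| q | coded 0 (c = 0) | coded 1 (c = 1) |
|---|---|---|
| 30% | 0.84/(0.70 + 0.84) = 0.55 | 0.21/(0.70 + 0.21) = 0.23 |
| 50% | 1.00/(0.50 + 1.00) = 0.67 | 0.25/(0.50 + 0.25) = 0.33 |

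Simulation with 400,000 patients, under two other answer distributions, agreed with the formula for c = 0. With answers skewed low (mean 2.23), r was 0.23 at q = 10% and 0.64 at q = 60%. With uniform answers it was 0.31 and 0.73. Among patients to whom both items applied, r was about 0.

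**3. Item ranking.** An item averaging 3 among those it concerns, and marked 0 by half the sample, averages 0.5 × 3 + 0.5 × 0 = 1.5. With the 0 excluded it stays at 3.

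**4. The 80% rule.** 0.80 × 21 = 16.8, so at least 17 items are needed. If a 0 does not count as completed, four zeros are tolerated. A fifth leaves 16/21 = 76% and no total score. Treating 0 as missing therefore also needs a stated rule.

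**The case against.** **The article never says that a 0 is scored.** This stands. 'Completed' is not defined, the form itself (Table 1) is not visible, and a 'not applicable' tick could be handled as unanswered. The distortions are conditional on the literal reading.

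**The 1 to 5 description belongs to the English version.** It does, so sections 2.7 and 2.10 are unlinked rather than flatly contradictory. Likewise, the remark "all items applicable to enrollers and non-enrollers alike" might be read as a claim that every item applies to every patient. It concerns enrolment status only and says nothing about employment, so it is not evidence of a contradiction.

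**A condensed article may leave recoding to another document.** This has some force. But the article does fix a scoring rule, a completeness rule and a factor method, and it reports a change to the instrument that those rules do not accommodate.

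**A lower total for an absent barrier is partly right.** This also stands. On a 1 to 5 form, a patient without a job might well have answered 1 to a work item, so the fairer comparison is often 0.095 rather than 0.19 to 0.24. The table above likewise shows that part of the induced correlation remains under a code of 1.

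Two stronger readings are tempting and not supported:

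- *That the planned t test by work status would be falsely significant in 54 to 93% of samples.* This uses the drop of 0.190 to 0.238 with an assumed total-score SD of 0.6 to 0.8 (d = 0.24 to 0.40) and 150 patients per group. It supposes that every non-employed patient marks two items and no employed patient marks any. Against a code of 1, d = 0.12 to 0.16 and the figure is about 18 to 28%. None of the shares or SDs is in the article.
- *That treating 0 as missing would push the sample below 210.* That needs more than 30% of 300 patients to mark a 0 and listwise deletion, which no section specifies. At 600 recruits, or against the lower bound of 105 with 300 recruits, it would take more than 65% (210/600 = 105/300 = 35% remaining).

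**Conclusion.** The point holds as an unadapted scoring rule: a nominal answer sits at 0 on the scale, and neither the scoring nor the analyses say how to treat it. If it is scored as written, the totals of patients with inapplicable items fall, correlations rise among items that share inapplicability, and those items drop in the ranking of key barriers. The inflated correlation is not general to all items; it needs items that do not apply to the same patients. The documents do not support saying that these effects will occur. They also fix no size, since the number and wording of the work items, the shares, the means and the SDs are all assumed; only the 1/21 = 0.048 per zero against a code of 1 is free of those assumptions. Item responses can be recoded at any time before analysis, so this is a should-fix.

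**What to change.** Add the following to the scoring text in section 2.7 and carry it into section 2.9:

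- Declare 0 a non-numeric code, left out of both numerator and denominator of total, subscale and item means.
- State that it counts as answered for the 80% rule.
- Run the factor analysis and alpha on the 1 to 5 responses, with pairwise or full-information handling of 'not applicable'.
- Add one sensitivity analysis that recodes 0 to 1, meaning barrier absent.
- Report the 'not applicable' rate for each item.

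The cost is a few sentences and one extra run, with no new data. The small downside is that totals will rest on slightly different item sets across patients; the per-item rates will show how far this goes.
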